**Methods:**

For aim 1, we will invite completers from our efficacy trial to participate in qualitative interviews. We will use data from these interviews to adapt the content of the live video program for asynchronous delivery and understand how to create a user-friendly format for an engaging web platform. For aim 2, we will enroll eligible participants recruited for the efficacy trial who could not enroll because of treatment barriers. Eligible participants will complete QoL, depression, anxiety, pain, treatment satisfaction, and program credibility measures at baseline and posttest. Inclusion criteria are identical to those for the efficacy trial, including stress and coping difficulties (self-report), no change in antidepressant medication in the past 3 months, no psychotherapy in the past 3 months, no major upcoming surgeries in the next 12 months, English speaking, ability to complete questionnaires on the web and participate in live video interventions, and consent before participation. The primary outcomes are feasibility, treatment satisfaction, and credibility. The secondary outcomes include physical, psychological, social, and environmental QoL; depression; anxiety; pain intensity; and pain interference. We will enroll at least two group cohorts and iteratively refine the program based on participant feedback after each cohort completes the open pilot trial.

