### Objective

The purpose of this study is to develop the first web-based platform of a mind–body program for adults with NF with stress and difficulties in managing NF symptoms. Our first aim (aim 1) is to adapt the adult mind–body program, 3RP-NF, for web-based delivery using qualitative data from semistructured interviews with participants who completed the efficacy trial. To achieve this aim, we will collect information about the participants’ experiences, perceptions of a web-based platform, and willingness to participate. We will use this information to develop a web-based platform—Neurofibromatosis Web (NF-Web)—that will be designed to be compatible with desktops, laptops, and mobile devices (eg, smartphones and tablets). We expect that participants from the efficacy trial will be willing to participate in semistructured interviews and provide meaningful feedback to inform the adaptation of the 3RP-NF intervention for web-based delivery. Our second aim (aim 2) is to optimize NF-Web through at least two subsequent open pilot studies with exit interviews. For each open pilot, we aim to optimize the feasibility and acceptability of NF-Web and explore the quantitative outcomes. We hypothesize that the final iteration of NF-Web will meet the a priori set feasibility and acceptability benchmarks [8-10]. We also hypothesize that participation in NF-Web will be associated with improvement in quantitative outcomes from baseline to posttest.

Related to the aims and scope of this pilot study, we will not be testing the use of different technologies for NF-Web delivery (eg, mobile and tablet vs desktop or laptop modalities); nor are we directly interested in the acceptability of such technologies (eg, the advantages of the website over the live video program). Rather, we are interested in studying the psychosocial program itself as a web-based tool to deliver the mind–body program to participants who typically have a higher burden when accessing psychosocial care. The creation of NF-Web essentially involves taking an efficacious program, which is delivered either in person or through live video by a trained clinical psychologist, and making it more accessible by delivering it through a web-based platform. Here, we describe our methodology for both the study aims.

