**Inclusion Criteria**
Diagnosis of neurofibromatosis (NF; NF1, NF2, or schwannomatosis)Adults aged 18 years or olderFull understanding of the informed consent process, study procedures, and assessments in English≥Sixth grade reading level (self-report)Difficulties coping with NF symptoms (self-report)Score≥6 on the 4-item Perceived Stress Scale

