Treatment satisfaction	The Client Satisfaction Questionnaire [24] assesses patient satisfaction with the web-based program.	Primary	Posttest
Treatment credibility	The Credibility Questionnaire [25] assesses how believable, convincing, and logical patients perceive the web-based program to be.	Primary	Posttest

^a^WHOQOL-BREF: World Health Organization Quality of Life Instrument, Short Form.

^b^*DSM-5*: *Diagnostic and Statistical Manual of Mental Disorders-5*.

We will send the participants a secure link through REDCap [15] to complete baseline assessments within a week of beginning the intervention. If a consented participant does not complete the questionnaires after a week of being sent the link, we will contact the participant and assist them in completing the questionnaires over the phone. The participants will also be sent weekly surveys throughout the program with less strict enforcement of assessment adherence owing to the aim of feasibility testing and because these time points do not affect primary or secondary outcomes. The participants will be emailed a reminder within 24 hours of the final session to complete the posttest assessments, and the CRC will call within three days if they have not completed the assessments. If a participant does not complete the posttest measures, the PI will continue contact attempts through phone and/or email as needed within two weeks of completing the last session. Any participants who are unreachable by the second full week (ie, 14 days) after posttest administration will be deemed lost to follow-up. We will conduct exit interviews lasting approximately 15 minutes at the participants’ convenience to gather feedback on their participation, including suggestions for program improvements, barriers and facilitators of program engagement, and the internet device they used to access the program (eg, mobile and tablet vs desktop).

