### Data Analysis

For aim 1, we will transcribe and analyze qualitative data from participants using NVivo 10 qualitative data analysis software (QSR International) [26]. Each interview will be transcribed and coded after the collection. We will use a thematic content analysis informed by framework [27] and inductive–deductive hybrid [28] methods. Themes will be extracted to inform the adaptations of NF-Web.

For aim 2, we will test feasibility according to the proportion of participants who agree to participate from those who express interest. Acceptability will be calculated as the number of participants who complete the web program and provide a posttest from those who start the program. We will assess the credibility of the web program using the Credibility Questionnaire (means, SDs, and IQRs) [25]. We will measure satisfaction with the web program using the Client Satisfaction Questionnaire (means, SDs, and IQRs) [24]. We will measure user experience with the User Experience Questionnaire (means, SDs, and IQRs) [23] and qualitative exit interview data. Upon completion, we will explore within-group improvements in NF-Web from baseline to posttest. Our hypotheses are that there will be positive within-group improvements in the secondary outcomes of NF-Web.

For our quantitative analyses, we plan to use linear contrasts to compare changes in secondary (QoL, emotional distress, pain) variables from baseline to posttest within the NF-Web intervention. For QoL outcomes that have established minimal clinically important differences [29], we will consider improvements from baseline to posttest to be clinically meaningful if the mean improvement is above 6.25.

We expect to use SPSS 25 software (IBM Corporation) for the statistical analyses, with an analytic strategy that mirrors the efficacy trial [11]. As our study is a small open pilot trial, we will not be adequately powered to detect within-group or between-groups differences for quantitative outcomes. We will also not be able to examine demographic variables beyond their descriptive aspects. Even so, baseline to posttest will be explored for each outcome in NF-Web, with descriptive statistics and signals of improvement being reported as relevant. If the NF-Web program confirms the primary outcomes (feasibility or acceptability) and trends positively for the secondary outcomes, we will consider this to be preliminary evidence that NF-Web is a useful psychosocial web-based program.

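### The success rule accepts feasibility or acceptability plus an undefined positive trend, which conflicts with the article's own hypothesis and its declared primary outcomes

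*Protocol article*

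**What the plan says.** The rule is the last sentence of Data Analysis: "If the NF-Web program confirms the primary outcomes (feasibility or acceptability) and trends positively for the secondary outcomes", then "we will consider this to be preliminary evidence that NF-Web is a useful psychosocial web-based program". The same paragraph concedes that "we will not be adequately powered to detect within-group or between-groups differences for quantitative outcomes".

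Data Analysis defines the two measures in the rule as different proportions. Feasibility is those who agree to take part, out of those who express interest. Acceptability is those who finish the program and give a posttest, out of those who start.

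The Objective sets the hypothesis: "We hypothesize that the final iteration of NF-Web will meet the a priori set feasibility and acceptability benchmarks".

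On the outcome hierarchy, the abstract's Methods paragraph says "The primary outcomes are feasibility, treatment satisfaction, and credibility". Table 1 gives the same status to two of these. The Client Satisfaction Questionnaire row reads "assesses patient satisfaction with the web-based program. Primary Posttest" and the Credibility Questionnaire row ends "convincing, and logical patients perceive the web-based program to be. Primary Posttest". Data Analysis plans means, SDs and IQRs for both.

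The abstract lists eight secondary outcomes: four QoL domains, depression, anxiety, pain intensity and pain interference. Data Analysis calls a mean QoL improvement above 6.25 clinically meaningful, but does not link that figure to the rule. Entry (Textbox 1) requires "Score≥6 on the 4-item Perceived Stress Scale".

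**The concern.** A success rule should give the verdict that the hypothesis and outcome list call for. This one departs from them in three ways.

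- **Or against and.** Uptake and completion can diverge. Under the rule, good uptake is enough for the primary part even if most starters drop out. The trend part would then rest on the minority who stayed to give a posttest, so failing acceptability also weakens the other half of the evidence.
- **Primary outcomes without influence.** Poor satisfaction or credibility scores cannot change the conclusion. Acceptability, which the abstract does not list as primary, can satisfy the primary part alone.
- **An undefined trend.** The direction of changes that the article says it cannot detect reliably becomes a condition for calling the program useful. What counts as a positive trend could be settled after the data are seen.

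What is at stake is a favorable summary of NF-Web that the stated hypothesis would not support.

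**Working it through.** The article states no error rate, power or alpha for the rule, so there is no figure to reproduce. The check sets the sections side by side, then asks how much the wording matters.

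**1. Status of each measure by section**

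| Measure | Abstract | Table 1 | Hypothesis (Objective) | Success rule |
|---|---|---|---|---|
| Feasibility | primary | not listed | must meet benchmark | enough alone for the primary part |
| Acceptability | not named as primary | not listed | must meet benchmark | enough alone for the primary part |
| Satisfaction | primary | primary | not named | absent |
| Credibility | primary | primary | not named | absent |
| QoL domains | secondary | primary | improvement expected | counted in the trend |

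**2. Or against and**

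Assumptions, none from the documents: the same benchmark *b* (70 to 80%) and the same true rate *p* for both measures, 40 people expressing interest, and independence. The 30 starters are the planned total.

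- a = P(X ≥ 30b), X ~ Bin(30, p), rounding the threshold up
- f = P(Y ≥ 40b), Y ~ Bin(40, p)
- or = 1 − (1 − a)(1 − f); and = a × f

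Worked case, b = 0.80 and p = 0.70: at least 24 of 30 gives a = 0.160, and at least 32 of 40 gives f = 0.111. Then or = 1 − 0.840 × 0.889 = 0.253, and = 0.160 × 0.111 = 0.018.

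| b | both rates 10 points below: or / and | both rates at benchmark: or / and |
|---|---|---|
| 70% | 0.282 / 0.023 | 0.826 / 0.340 |
| 75% | 0.230 / 0.015 | 0.798 / 0.300 |
| 80% | 0.253 / 0.018 | 0.840 / 0.360 |

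**3. Chance of a positive trend with no true change**

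For one outcome, or for the average of all eight, the mean change is equally likely to be positive or negative. The chance is 0.50 at any sample size.

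For eight independent outcomes the count of positive changes is Bin(8, 0.5):

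- all eight: 0.5^8 = 1/256 = 0.004
- any one: 1 − 1/256 = 0.996
- at least five: (56 + 28 + 8 + 1)/256 = 93/256 = 0.363

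Correlated outcomes were simulated as equicorrelated normals (400,000 replicates, assumed correlation 0 to 0.7):

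| Reading of the trend | Correlation 0 | 0.3 | 0.5 | 0.7 |
|---|---|---|---|---|
| any one of 8 | 0.996 | 0.947 | 0.889 | 0.807 |
| at least 4 | 0.638 | 0.577 | 0.556 | 0.538 |
| at least 5 | 0.365 | 0.424 | 0.444 | 0.462 |
| at least 6 | 0.145 | 0.277 | 0.333 | 0.383 |
| all 8 | 0.004 | 0.052 | 0.111 | 0.194 |

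These figures are upper bounds for the whole rule, which also needs feasibility or acceptability. That part does not depend on efficacy, so the bound is nearly reached when uptake or completion is good.

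**4. What a magnitude criterion would change**

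Take the 24 posttest completers reported in Results and an assumed SD of change of 10 to 20 on the scale of the 6.25 criterion. With no true change, P(mean change > 6.25) = 1 − Φ(6.25√24/SD), which is 0.001 at SD 10 and 0.063 at SD 20. For a single QoL outcome, a bare sign criterion gives 0.50. The unstated definition therefore decides how much the trend can show.

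**The case against.** The strongest defense is that the rule claims little. Its conclusion is preliminary evidence from an open pilot that admits low power. Baseline-to-posttest changes are described as exploratory, and the Conclusions look to future trials. Results ties dissemination to the fully powered efficacy trial. Results also reports 24 posttest completers against a recruitment goal of 30 that was met, which is 24/30 = 80% if all 30 started, so mass abandonment does not seem to have happened. This stands, and it limits the severity. It does not remove the conflict between the rule and the hypothesis. The efficacy trial tests the live video program, so it does not replace evidence on NF-Web.

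Some stronger readings are tempting, but the article does not support them:

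- **The rule as a whole is a coin flip or better when nothing works.** The 50% belongs to the trend part, and only for one outcome or an average. It is lower for at least five of eight (0.37 to 0.46) and far lower if all eight must improve (0.004 to 0.19).
- **A trend means any mean change above zero.** The article does not say so. Its linear contrasts and the 6.25 criterion could have been meant to inform the judgment, though the rule refers to neither.
- **Regression to the mean must inflate the changes by a known amount.** Selection is on a stress score taken at screening, which is not among the outcomes in Table 1, and baseline is a separate assessment. The shift depends on how much more strongly the screening score correlates with baseline than with posttest, and it is zero if the two correlations are equal. The documents give neither.
- **The benchmarks are missing.** Their values may be in the full protocol, so their absence from the article is not counted.

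**Conclusion.** The point holds as a should-fix.

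Three parts rest on the text alone: the rule accepts one of two measures where the hypothesis needs both, it leaves out two declared primary outcomes, and its trend condition has no definition.

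The size of the first part depends on assumptions. With benchmarks of 70 to 80%, 30 starters, 40 interested people and independence, a program 10 points below both benchmarks passes the primary part 23 to 28% of the time under *or*, and about 2% under *and*.

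For the trend, the finding is that its error rate cannot be determined. With no true change it is 50% for one outcome or an average, and anywhere from under 1% to over 99% for eight independent outcomes, depending on the reading. Without a control group and with entry on raised stress, some improvement may also occur without a program effect, but the documents do not allow that to be quantified.

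A reader might infer that the article makes an unsupported efficacy claim. It does not, since the conclusion is explicitly preliminary.

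**What to change.** In the last paragraph of Data Analysis:

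- Require feasibility **and** acceptability, to match the Objective.
- Make the rule consistent with the declared primary outcomes by including satisfaction and credibility against whatever a priori benchmarks the full protocol holds. The abstract, Table 1 and the rule should give the same primary list, including the status of QoL.
- Remove the positive trend from the decision rule. Report each pre-post change as a descriptive estimate with a 95% confidence interval, and note the uncontrolled design and the selection on stress.
- Limit the conclusion to whether a controlled trial of NF-Web is warranted.

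The cost is a few sentences and no new data. A favorable conclusion becomes somewhat harder to reach. If the full protocol holds no satisfaction or credibility benchmarks, the article should say so and state that these outcomes are descriptive only, because thresholds chosen after the data are seen would not be a priori. Results places completion of the analyses in October 2021, so the change should be dated and made before the outcomes are examined.

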### Data Management

We will store the collected data in a secure location on computers with password protection to maximize confidentiality and security. We will assign each subject a unique, anonymous identifier that is associated with all collected data, including questionnaires and subject-completed logs. Any paper data files will be stored in a secure, locked location that is only accessible to the study team, and these files only include coded subject identification. In addition, all electronic questionnaire data are stored on REDCap [15], a web-based, Health Insurance Portability and Accountability Act–compliant data system available through our academic medical center.

## Results

The NF-Web open pilot clinical trial is ongoing. As of April 2020, we completed the qualitative interviews (n=23) and analyzed the data to construct the first version of the website for our open pilot study. We successfully recruited both cohorts of patients to participate in the trial with the goal of recruiting 30 individuals in total being met (n=24 completed posttest after completing the program). We ended the open pilot trial in May 2021. We aim to complete data analyses by October 2021 and then prepare NF-Web for dissemination in accordance with the results of the fully powered efficacy trial for adults with NF.

## Discussion

### Comparison With Prior Work

Patients diagnosed with NF have a lower but modifiable QoL. Virtual mind–body interventions developed to improve stress management and QoL in people with NF are feasible, acceptable, and beneficial [3,5,6]. However, most patients with NF still struggle to access specialized, evidence-based psychological treatment, even with virtual adaptations. This paper describes the study design and specific strategies used to conduct qualitative interviews with adult patients diagnosed with NF from our ongoing efficacy trial to inform the development of a novel web-based platform to teach resiliency skills and stress management to improve QoL in people with NF. We provide details on the protocol and the potential benefits and challenges of delivering psychosocial care using a web-based platform. We also discuss the methods of monitoring and addressing participant progress and safety throughout the program.

This protocol presents a novel method for delivering care to patients with rare diseases across the globe and provides invaluable information for future trials using asynchronous platforms to deliver psychological care. The web-based program retains the evidence-based mind–body skills associated with improved QoL and psychosocial functioning [11], while providing a cost-effective and scalable delivery modality that could be implemented effortlessly with few human resources. In addition, all program materials could be seamlessly delivered through the website with cumbersome aspects of the live program (eg, homework submission, materials, and resources) found in 1 place. In the future, this program could also be easily translated and culturally adapted for delivery to non–English-speaking patients with NF worldwide. Video content can also be designed to have download capability so that individuals with low broadband connections can store the videos locally on their devices and watch without interruption. Such web-based programs have been developed for other medical populations with a psychosocial profile similar to that of NF (eg, chronic pain, diabetes) [26,27] and have been shown to be feasible, accepted by patients, and in some cases as effective as virtual or in-person interventions [30]. NF-Web represents a potential first-line treatment for patients with NF-specific psychosocial difficulties.

Similar to the DoD trial, we aim to implement and disseminate NF-Web in conjunction with the live video program throughout NF centers across the world, as well as through the Children’s Tumor Foundation (CTF) and local foundations. This program addresses the need for programs that require greater human resources to be addressed by streamlining psychosocial treatment for adults with NF. The web-based treatment model can be used to inform other populations within the NF community (adolescents, families), as well as other medical illness populations.

### Strengths and Limitations

Even with adaptation, there are limitations to consider in the proposed study. First, diverse recruitment poses a barrier to the generalizability of the findings. Previous trials, including our adult efficacy trial, have enrolled mostly middle-class, higher-educated White female patients. We hope that with stronger relationships and involvement from foundations within the NF community, we can maximize opportunities to recruit diverse patients. Although a geographically diverse sample may have its own limitations (eg, differences between geographic regions and major language differences), it also serves as a strength of the program by promoting more flexibility (eg, participants are not bound to a schedule and can participate in their own time) not seen in the live video program. Our use of a geographically diverse sample is consistent with our other NF trials. Second, the live video program is only available in English. Recorded video offers opportunities to provide multilingual subtitles, which can aid program delivery; however, verbal and written materials are currently offered in English only, which limits the individuals who may participate. Finally, although the rationale is to develop a program that can be inclusive of people with barriers to live virtual psychosocial treatment (eg, scheduling, appearance concerns), there are other barriers for participants that NF-Web will not address yet, including participants without technology resources or those with limited financial means.

